# 1. Introduction

## 1.1 Background

Dysmenorrhea can be described as painful uterine cramps of menstrual origin (1). Dysmenorrhea can be classified as primary or secondary. Primary dysmenorrhea (PD) is pain in the absence of any organic cause and is most common in women under the age of 25, with pain starting within three years of menarche (2,3).Characteristic symptoms of primary dysmenorrhea are crampy, colicky spasms of pain in the suprapubic area occurring within 8-72 hours of menstruation and peaking within the first few days as menstrual flow increases (1,3,4). In addition to painful cramps many women with primary dysmenorrhea experience back and thigh pain, headaches, diarrhea, nausea and vomiting (1,3).

Between 43-91% of women under 20 (5) and 16.8 – 81% of women of reproductive age (6) experience dysmenorrhea and is a leading cause of regular absence from school or work amongst reproductive aged women (7) and reduced classroom or academic performance amongst Australian adolescents (8) and is thought to cause significant economic impact (9).

Common biomedical treatments are Non-Steroidal Anti Inflammatory drugs (NSAIDs) such as ibuprofen and the Combined Oral Contraceptive (COC) (2,10)These interventions are effective for many women however there are significant adverse events associated with both interventions (10,11) with regular monthly ingestion raising concerns about long-term risks in NSAIDs (12-14).

While NSAIDs and COC are effective for many women approximately 25% of women have pain that is refractory to either of these standard treatments (15,16)

*Acupuncture*

Complementary and Alternative medicine (CAM) is commonly used by women in Australia and New Zealand with chronic, unresolved health problems (17-21). Given the chronic nature of dysmenorrhea and the fact that many women are not receiving significant symptom resolution from standard therapies it is logical that many women with dysmenorrhea would be interested in CAM.

Traditional Chinese Medicine (TCM) based Acupuncture is a popular and common form of CAM with many women using acupuncture treatment for gynecological issues (22)

*Acupuncture as a complex intervention:*

Acupuncture, in common with many other Complementary and Alternative or non-pharmacological therapies, is a complex intervention (23-26). The Medical Research Council (MRC) defines complex interventions as “built up from a number of components, which may act both independently and interdependently” (27,28)

A typical acupuncture consultation includes but is not limited to: history taking, self care and lifestyle advice, TCM diagnosis and explanation, palpation of the pulse and other parts of the body, observation of the tongue, insertion and manipulation of needles, as well as common co-modalities such as moxibustion and cupping (23,29,30).

There is some evidence that the advice given during the acupuncture treatments and the way that the advice is delivered is an important component of the clinical outcome, however its role in outcomes in the treatment of dysmenorrhea is unclear (31-33).

*Acupuncture treatment of Dysmenorrhea*

The most recent systematic reviews have found conflicting results in the effectiveness of acupuncture in the treatment of dysmenorrhea (34).

One large scale pragmatic trial (35) showed a significant reduction in menstrual pain and an increase in quality of life in women undergoing acupuncture treatments over a three month period compared to women having only usual care. This trial did not document components of the treatment or frequency of treatment and therefore it is impossible to determine what components of the acupuncture treatment contributed towards the positive outcome. There is conflicting evidence in the literature on role of dosage and stimulation style in improving clinical outcomes of acupuncture treatment of dysmenorrhea. Chinese based literature shows very positive results with higher frequency of treatment (36-39) and with the usage of electroacupuncture (40-43). However these are tempered by poor methodological quality (44) and by acupuncture treatments that do not represent clinical practice in Australia and New Zealand (unpublished data from thesis) and other western countries (45).

In addition to measuring outcomes for symptoms of dysmenorrhea women who complete the trial will be invited to take part in semi-structured interviews that will examine the acceptability of the differing interventions, the importance of the explanations and advice given by the practitioners as well as their experience in the trial itself.

*Methodological challenges:*

Recent papers from CAM experts (46) acupuncture researchers (29,47)and acupuncture practitioners (45,48) all emphasise the vital need for research to reflect and inform clinical practice.

This trial uses a mixed methods approach with a pragmatic framework (49) that allows trial design to be informed by both survey and focus group data that has been collected as part of this thesis. This allows a randomised controlled trial to be developed that accurately reflects a clinically relevant setting. To achieve a balance between a tightly and loosely defined intervention is an important consideration in evaluating acupuncture as it is delivered in a community setting (25). A manualised protocol has been developed from the data from practitioner interviews and focus groups to help achieve this balance. This manualisation has been successfully used in previous acupuncture trials to ‘distill’ expert advice into a form that allows both individualisation and reproducibility (26,50,51). This manualisation will allow the exploration of individual contributions of frequency and stimulation style by reducing the 'noise' present in the trial while still staying faithful to the theoretical framework that underpins TCM acupuncture (23,24). In addition it is important that the study documentation and protocol conforms to the guidelines set out by Smith and colleagues (2011) that discuss the importance of reporting different components of the acupuncture treatment (52).

## 1.2 Study Rationale

This project will increase the evidence base on the effectiveness of treating primary dysmenorrhea with acupuncture based on a trial design that closely mimics clinical practice in Australia and New Zealand. The primary focus of this trial is the contribution of two theoretically important components of acupuncture ‘dosage’, frequency of treatment and type of needle stimulation, to the clinical outcomes. In addition the follow up interviews will allow women to have a qualitative ‘voice’ on their experiences as part of the trial.

# 2. Study Objectives

The primary aim of this project is to examine the effect of changing frequency and type of stimulation on the symptoms of primary dysmenorrhea.

The specific questions that this project address are:

1. Does using a manualised protocol based on current clinical experience provide a positive outcome with symptoms of primary dysmenorrhea?
2. What extent do differing frequencies of treatment and types of stimulation contribute to that effect?
3. Is acupuncture, especially in more frequent treatments, an acceptable intervention for participants ?
4. Does TCM acupuncture change study participants perceptions of health and illness with respect to dysmenorrhea ?
5. What other components of the acupuncture treatment are important to study participants ?

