## 5.2 Screening for eligibility:

Initial screening will be undertaken over the phone by the researcher. Women who meet the eligibility criteria and are interested in joining the study will be met in person if they are located in Auckland or further information will be given via post or email if in Wellington. Prior to trial entry but post consent potential participants will be asked to fill in a menstrual pain diary that will be used to prevent recall error and validate that the participants do have maximum/peak pain greater than or equal to 3/10 and that this pain occurs just prior too, or in the first three days of menses. If these participants are eligible and are randomized then this data will become the baseline data.

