5.5.2 Treatment allocation

Randomization will be into one of four study groups:

High Frequency – Manual stimulation: Women randomly allocated to this group will receive 3 acupuncture treatments in the 7 days prior to menses and 1 acupuncture treatment in the first 3 days of menses. Stimulation will be provided by manual acupuncture, achieving DeQi upon needle insertion. Subsequent stimulation based on practitioners differential diagnosis. Needles will be retained for 20-30 minutes

High Frequency – Electro acupuncture stimulation: Women randomly allocated to this group will receive 3 acupuncture treatments in the 7 days prior to menses and 1 acupuncture treatment in the first 3 days of menses. Stimulation will be provided by Electro-Acupuncture, achieving DeQi upon needle insertion. Subsequent stimulation will be using a 2/100Hz waveform for 20-30 minutes.

Low Frequency – Manual Stimulation: Women randomly allocated to this group will receive 3 acupuncture treatments in the 3 weeks prior to menses (1/week) and 1 acupuncture treatment in the first 3 days of menses. Stimulation will be provided by manual acupuncture, achieving DeQi upon needle insertion. Subsequent stimulation based on practitioners differential diagnosis.Needles will be retained for 20-30 minutes

Low Frequency – Electro acupuncture stimulation: Women randomly allocated to this group will receive 3 acupuncture treatments in the 3 weeks prior to menses (1/week) and 1 acupuncture treatment in the first 3 days of menses. Stimulation will be provided by Electro-Acupuncture, achieving DeQi upon needle insertion.Subsequent stimulation will be using a 2/100Hz waveform for 20-30 minutes.

5.5.3: Withdrawal procedures

If a participant wishes to withdraw from the trial they will be immediately removed from treatment. The most recent menstrual pain diary will be used and they will be requested to complete an SF-36.

If a participant withdraws during intervention they will not be replaced however if they withdraw post randomization but prior to the first treatment they will be replaced.

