# 6. Investigational therapy and controls

## 6.1 Acupuncture

A total of 12 treatments over 3 menstrual cycles will be administered according to the frequency specified in the subjects’ group allocation. The study acupuncturists will include the primary investigator ([name]) and all study acupuncturists will be experienced, with a minimum of a Bachelors level qualification in Acupuncture and will hold a current annual practicing certificate with a relevant professional acupuncture body. Practitioners will be located in Auckland and Wellington, New Zealand. [name] will also be involved in training and quality control of other study acupuncturists.

Following the first phase of this mixed methods PhD thesis a trial protocol has been developed based around using a manualised version (50) of standard acupuncture treatments which has been designed in consultation with experienced practitioners through interviews and focus groups.

This manualisation allows considerable flexibility, in order that the treatment can match patient variability. The protocol is not too broad, such that “anything goes” as this would mean that it would be more difficult to attribute any impact of treatment to the different interventions we are using, frequency and stimulation of treatment. The protocol is also not too narrow, as we want the treatments to reflect how acupuncturists normally work in clinical practice. This is an important consideration in designing a clinically relevant intervention (25).

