## 6.2 Control group

There is no control group in this study as it is designed to examine the differing contribution of different acupuncture components to the clinical outcome.

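### Objective 1 asks whether the acupuncture protocol works, but with four active arms and no control the trial can only describe before-after change

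*Protocol*

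**What the plan says.** Protocol section 2 states the primary aim as a comparison of components: "The primary aim of this project is to examine the effect of changing frequency and type of stimulation on the symptoms of primary dysmenorrhea". It then lists specific questions. The first is about the treatment as a whole: "Does using a manualised protocol based on current clinical experience provide a positive outcome with symptoms of primary dysmenorrhea". The second asks how far frequency and stimulation contribute to that effect, so it takes for granted that the first has been answered. Section 1.2 opens with "This project will increase the evidence base on the effectiveness of treating primary dysmenorrhea with acupuncture" and goes on to name the two dosage components as the primary focus.

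Section 5.5.2 defines four arms, high or low frequency crossed with manual or electro stimulation, all with real needling. Under section 6.1 every arm is treated to the manual, with 12 treatments over 3 cycles. Section 6.2 says: "There is no control group in this study as it is designed to examine the differing contribution of different acupuncture components to the clinical outcome".

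Section 5.2 uses a pre-entry diary to confirm peak pain of at least 3/10 and adds: "If these participants are eligible and are randomized then this data will become the baseline data". The primary endpoint (section 8) and the sample size (section 9.1) both concern a 20% difference in average pain between groups. Section 9.2 plans a two-way repeated measures ANOVA.

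**The concern.** The reason given in section 6.2 for having no control group fits objective 2, because randomised arms can show how components differ. It does not fit objective 1, which asks about an absolute effect. The protocol gives objective 1 no untreated, sham or usual-care comparator, no external benchmark, no second untreated cycle, and no statement that it is descriptive only.

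What remains is the fall from baseline. That fall mixes any treatment effect with natural variation between cycles, expectation (every woman knows she receives acupuncture), changes in analgesic or other co-intervention use, and some regression to the mean, since the diary that had to pass the screen is also the starting value. At stake is what the trial may conclude: a fall in pain could be read as a yes to objective 1 when the design cannot tell why pain fell.

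**Working it through.** **Which question the design can answer**

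| Question | Comparison needed | Available in the design |
|---|---|---|
| Objective 2: contribution of frequency and stimulation | Arm against arm | Yes, randomised |
| Objective 1: does the protocol give a positive outcome | Protocol against no protocol, or a stated benchmark | No; only change from baseline |

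The protocol gives no figure for objective 1, so there is none to reproduce. The size of one component, regression to the mean, can be bounded.

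**Inputs**
- Screening threshold: 3 on the NRS, applied to peak pain (section 5.2).
- SD: 1.3 (section 9.1). An SD of 2.0 is added as an assumption.
- Women analysed: 60 (section 9.1, before the 10% allowance for loss).
- Unselected mean of 4 to 5 and between-cycle correlation r of 0.4 to 0.8: assumptions, as the protocol gives neither.

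**Formulas**
- Expected fall with no treatment effect: (1 − r) × SD × φ(z) / (1 − Φ(z)), with z = (3 − mean) / SD.
- 95% half-width for mean change: 1.96 × SD × √(2(1 − r)) / √60.

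The half-width uses the unselected SD at both times, which is an approximation.

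**Worked example**, mean 4, SD 1.3, r 0.5: z = −1/1.3 = −0.769; φ(z)/(1 − Φ(z)) = 0.2968/0.7791 = 0.381. Expected fall = 0.5 × 1.3 × 0.381 = 0.25. Half-width = 1.96 × 1.3 × √1 / 7.746 = 0.33.

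**Results, with the same SD and r on both sides**

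| Mean | SD | r | Expected fall | Half-width |
|---|---|---|---|---|
| 5 | 1.3 | 0.8 | 0.03 | 0.21 |
| 5 | 1.3 | 0.5 | 0.09 | 0.33 |
| 4 | 1.3 | 0.5 | 0.25 | 0.33 |
| 5 | 2.0 | 0.5 | 0.29 | 0.51 |
| 4 | 2.0 | 0.5 | 0.51 | 0.51 |
| 4 | 2.0 | 0.4 | 0.61 | 0.55 |

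Over this range the expected fall reaches the half-width only at mean 4, SD 2.0 and r of about 0.5 or below. A smaller shift still raises the chance of a significant fall above the nominal 2.5% in that direction. That chance is Φ(fall/SE − 1.96), where SE = half-width/1.96. It is about 7% for mean 5, SD 1.3, r 0.5; 31% for mean 4, SD 1.3, r 0.5; and 58% for mean 4, SD 2.0, r 0.4.

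**From peak to average pain.** The screen is on peak pain and the endpoint is average pain, so the artefact carries over only in part. If the two correlate at 0.8 (assumption) and have a similar SD, multiply by 0.8: the largest case becomes 0.8 × 0.61 = 0.49, below its half-width of 0.55.

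**The case against.** The strongest reply is that the protocol already places its inference where it should. The primary aim, the primary focus in section 1.2, the endpoint, the sample size and the reason given in section 6.2 all concern differences between components. Regression to the mean and natural course are expected to be equal across randomised arms, so those comparisons are not biased. This stands, and it limits the point to objective 1 and the wording of section 1.2.

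Four stronger readings are tempting and are not supported:
- A reader might infer that any fall from baseline will be reported as benefit. The protocol does not say how objective 1 will be judged, and section 9.2 does not tie a time effect to it. An analysis plan may settle that, although it cannot supply a missing comparator.
- A reader might infer that regression to the mean alone would produce a significant result. With matched assumptions that is the expected outcome only in one corner of the range, and less so for average pain. Section 4.3 also requires recalled pain of at least 3 in two of the past three cycles, so the diary probably removes few women.
- A reader might infer that free analgesic use lowers later scores. Section 6.3.1 has women continue their medication and use analgesics as needed; it introduces nothing new after baseline. Use is recorded at baseline and in the diary (section 8). Only a change in use matters, and its direction is unknown.
- A reader might infer that the reuse of the screening diary is hidden. Section 5.2 states it openly.

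It can also be said that a positive outcome need mean no more than improvement. If so, the objective should say that, because section 1.2 uses the word effectiveness.

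**Conclusion.** The point holds, as a mismatch between one stated objective and the design. Objective 1 is a question of absolute effect, and the trial has only uncontrolled before-after change with which to answer it. This conclusion follows from the text and needs no assumption.

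The main difficulty is that several causes of change cannot be separated without a comparator. Regression to the mean is a secondary part, about 0.03 to 0.6 points on peak pain against matched half-widths of about 0.21 to 0.55, and smaller on average pain. Those figures rest on the assumed mean, correlation and upper SD. The primary aim, objective 2, the endpoint and the sample size are untouched.

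**What to change.** Reword objective 1, for example: *To describe change from baseline in menstrual pain and SF-36 in each arm, with 95% confidence intervals; no inference on effectiveness will be drawn because there is no untreated or sham arm.* Align the opening of section 1.2 with this, and limit inferential conclusions to the randomised contrasts of objective 2. Objective 2 should then no longer refer back to an effect that objective 1 is taken to have shown.

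The cost is wording only; arms, sample size, visits and primary analysis stay as they are. The downside is that the trial gives up an effectiveness claim, but its design cannot support that claim. Taking a separate untreated cycle as baseline would reduce regression to the mean but would leave the other explanations in place, so it is no substitute for the rewording.

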# 3. Study Design

A Phase III randomized controlled trial comparing 4 groups incorporating differing modes of stimulation and treatment frequency on pain and quality of life in women suffering from primary dysmenorrhea.

# 4. Study Population

## 4.1 Sample Size

68 women in total, 17 participants per study group

## 4.2 Recruitment

Local family planning clinics in Auckland and Wellington as well as Student health at local universities (University of Auckland and Victoria University,Wellington)

## 4.3 Inclusion Criteria

- Women with suspected or confirmed primary dysmenorrhea as defined by the following:
- Age 18-45 years
- Period pain started before the age of 18 OR Pain started > 18 but Ultrasound and Laparoscopy negative for secondary pathology.
- Pain greater than or equal to 3 out of 10 on a numeric rating scale during the first three days of menses for at least two of the past 3 menstrual cycles.
- Regular menstrual cycles (28 +/- 7 days) for the last three months.
- Understands spoken and written English
- Able to give informed consent

## 4.4 Exclusion Criteria

- Previous diagnosis of endometriosis or secondary dysmenorrhea.
- Abdominal Surgery in the previous 3 months
- Injectable or implant contraceptives (Depo provera, Jadelle, Murina ) within the last 3 months
- Oral Contraceptive usage started less than 3 months ago
- Chronic pain conditions ( >14 days per month with pain)
- Current mental health illness
- Neuropathic pain secondary to surgery
- Sterilisation

# 5. Participant selection and enrollment

## 5.1 Identifying participants

Recruitment:

A number of strategies will be used in progressive phases dependent on recruitment:

1. Posters will be placed in Family planning clinics and at Student health in local universities and 18-45 year old women presenting at these clinics with symptoms of period pain (dysmenorrhea) will be given an information sheet and contact details of the primary researcher.
2. Facebook advertisement and Facebook page promoting the study will be designed
3. If recruitment is still not sufficient at these sites then local PHO's such as Procare will be approached and GP's operating under the umbrella of these PHOs invited to assist in recruitment.

## 5.2 Screening for eligibility:

Initial screening will be undertaken over the phone by the researcher. Women who meet the eligibility criteria and are interested in joining the study will be met in person if they are located in Auckland or further information will be given via post or email if in Wellington. Prior to trial entry but post consent potential participants will be asked to fill in a menstrual pain diary that will be used to prevent recall error and validate that the participants do have maximum/peak pain greater than or equal to 3/10 and that this pain occurs just prior too, or in the first three days of menses. If these participants are eligible and are randomized then this data will become the baseline data.

## 5.3 Consenting participants

For those that consent and have an eligible menstrual pain diary a trial entry form will record baseline clinical data as well as demographic characteristics. Randomisation will occur after trial entry form completed.

## 5.4 Ineligible and non-recruited participants

Women who do not meet the initial eligibility criteria or whose menstrual pain diaries do not meet eligibility criteria will be logged. Women who decline to participate after initial contact will also be logged, with a reason for declining (if given).

## 5.5 Randomisation

5.5.1 Randomisation

Randomisation will be undertaken by using the secure internet website Sealed Envelope (Sealedenvelope.com). This will produced a randomization schedule with variable blocking.

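### A separate randomisation schedule for each city would be a cheap improvement: the protocol names no stratification factor, although practitioners, recruitment sources and enrolment route differ between Auckland and Wellington

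*Protocol*

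**What the plan says.** Section 5.5.1 gives the whole allocation method in two sentences. A web service is used, and it produces a "randomization schedule with variable blocking". Block sizes are not given and no stratification factor is named there or anywhere else in the protocol. Section 5.5.2 adds that "Randomization will be into one of four study groups", and section 4.1 sets "68 women in total, 17 participants per study group".

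Three features of conduct are tied to city:

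- **Recruitment source.** Section 4.2 lists "Local family planning clinics in Auckland and Wellington" and names a different university in each city.
- **Enrolment route.** Under section 5.2, eligible women "will be met in person if they are located in Auckland"; those in Wellington receive further information by post or e-mail. Section 11.2.1 allows consent face to face or by post.
- **Practitioners.** Section 6.1 states: "Practitioners will be located in Auckland and Wellington, New Zealand". City therefore in effect decides which acupuncturists can treat a woman.

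The analysis in section 9.2 names no city or practitioner term. It plans a two-way repeated measures ANOVA for NRS scores and a GLM regression on factors that influence them.

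**The concern.** A single blocked list keeps the four arm totals close to equal but does nothing to equalise the number of Wellington women per arm. With 17 women per arm, chance can leave the arms with visibly different city mixes. If the cities differ in outcome, through practitioners, type of participant or mode of enrolment, part of that difference enters the estimated effect of treatment frequency or stimulation type in this one trial. If city is also left out of the model, its variance stays in the error term.

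The allocation method has to be fixed in the protocol. A later statistical analysis plan could add a city term, but it could not change how women had already been allocated.

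**Working it through.** **Inputs from the protocol.** N = 68 in four arms of 17 (section 4.1), so 34 v 34 for each factor; SD 1.3 NRS units, 60 women before a 10% loss (section 9.1).

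**Assumptions, because the protocol gives no figure.** Wellington share 20%, 30% or 50%, that is K = 14, 20 or 34 of 68 women; a city difference d of 0.5 to 1 NRS point; block sizes drawn from 4/8 or 4/8/12.

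**The plan's own figure.** 60 / 0.9 = 66.7, rounded up to 67 and then to 68 for four equal arms. The stated 68 is reproduced.

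**Imbalance with one schedule.** If city is ignored at allocation and arms end at 17 each, the number of Wellington women per arm is hypergeometric, with variance 17 × (K/68) × (1 − K/68) × (51/67). For K = 20 this is 17 × 0.294 × 0.706 × 0.761 = 2.69, so the SD is 1.64. Simulating all four arms jointly gives:

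| | K = 14 | K = 20 | K = 34 |
|---|---|---|---|
| Mean gap, most v least loaded arm (women) | 3.4 | 3.9 | 4.2 |
| P(that gap is 4 or more) | 45% | 56% | 63% |
| Mean gap, one given pair of arms (women) | 1.9 | 2.1 | 2.3 |
| P(given pair differs by 4 or more) | 14% | 19% | 23% |
| Mean difference in city share, 34 v 34 | 8 points | 9 points | 10 points |
| 95th percentile, 34 v 34 | 18 points | 24 points | 24 points |

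Simulating actual permuted blocks instead of fixed arms of 17 gives nearly the same figures. At a 10% share (7 women) the problem is smaller: the extreme arms differ by 4 or more in about 19% of trials.

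**Effect on a factor contrast.** Shift = difference in city share × d.
- On average: 0.08 × 0.5 = 0.04 to 0.10 × 1 = 0.10 points.
- At the 95th percentile: 0.18 × 0.5 = 0.09 to 0.24 × 1 = 0.24 points.
- For scale, the standard error of a 34 v 34 comparison is 1.3 × √(2/34) = 0.32.

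**Variance explained by city.** p(1 − p)d² / 1.3², with p = K/68.
- d = 0.5: 0.164 × 0.25 / 1.69 = 2.4% (K = 14) to 0.25 × 0.25 / 1.69 = 3.7% (K = 34).
- d = 1: 0.164 / 1.69 = 9.7% to 0.25 / 1.69 = 14.8%.

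**With a schedule per city.** The mean gap between extreme arms falls to about 0.5 to 1.4 women, and the mean 34 v 34 difference in city share falls to about 1 to 3 points. The mean spread in total arm size rises from about 0.5–0.9 to about 1.0–2.0 women, because the last block in each city may be incomplete.

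**The case against.** The strongest reply is that nothing in section 5.5.1 is false, and that blocked randomisation without site strata is valid for 68 women. City mix is then random, and the significance level already allows for it. That stands: a reader might infer confounding or a biased comparison, but the design has neither.

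The size of any harm rests on an assumed city difference, since the protocol reports no city or practitioner effect on menstrual pain. It also works to limit one: manualised treatment, training by the primary investigator, a check of each practitioner, and needling standardised with a measuring device (sections 6.1, 8 and 10.1). In addition, the repeated measures analysis uses a baseline diary, so a constant difference in pain level between cities drops out of a group-by-time comparison; only a city difference in change would matter. These points limit the effect but leave the imbalance in place.

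A reader might also take support from section 1.1, which cites some evidence on advice given in treatment and says that "the way that the advice is delivered is an important component of the clinical outcome". The same sentence goes on to call its role in dysmenorrhea unclear, so it does not show a practitioner effect here and is not relied on.

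Finally, the city term in the model could be left to an analysis plan, and the planned GLM could carry it. That would recover much of the precision, but it would not balance the arms.

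**Conclusion.** The point holds as a low-cost improvement, not as an error. That there is no stratification is read from the protocol's silence on any factor; the protocol does not state it outright.

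A gap of several Wellington women is likely only between the most and least loaded of the four arms. It would be wrong to read this as any two arms differing that much: a given pair differs by about 2. For the factor comparisons that answer the primary aim, the expected shift is 0.04 to 0.10 NRS points under an assumed city difference of 0.5 to 1 point, well inside the standard error of 0.32. Even the upper figure of about 0.24 is below it. City would explain about 2% to 15% of the variance. All of this depends on the assumed Wellington share of 20% to 50%; a smaller share gives less imbalance.

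**What to change.** In section 5.5.1, state: *Randomisation will be stratified by city (Auckland, Wellington), with variable blocks within each city.* Include city as a factor in the NRS analysis, in section 9.2 or in the analysis plan.

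Before recruitment the cost is two lists instead of one, with N still 68. The change largely removes the imbalance but not wholly: about one woman remains between the extreme arms. Final arm sizes may vary by about one woman more. Stratifying by city does not balance practitioners within a city if a city has more than one, and the protocol does not give their number. Once recruitment has started, women already randomised cannot be rebalanced, and only the model term would still be available for them.
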